## Methods

### Study design and setting

The study is designed as a prospective, single-blind, multi-center, randomized controlled trial with four arms – three intervention groups versus a common control group of the participating optometry service providers (OSPs).

The study will be carried out in Guangzhou and Inner Mongolia, China. Guangzhou is the capital city of Guangdong Province, representing a well-developed metropolitan in the south of China. Inner Mongolia’s autonomous region has fewer medical resources, representing relatively underdeveloped land in China. We chose three cities in Inner Mongolia, which are Bayannur (west), Hohhot (central) and Xinganmeng (east). Optometry service providers (OSPs) are considered for inclusion if they meet the criteria defined below. In each location, we will draw a representative sample of eligible OSPs using stratified and simple random sampling.

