### Sample size calculation

We calculated the sample size based on the proportion of optometry accuracy, which is the primary outcome of this study. According to the previous literature [5], the proportion of optometry accuracy is 44.1% in the control group (receiving usual USP visits), and proportions in the intervention groups (receiving usual USP visits plus BVIs) are supposed to be 66.1% (when assuming the effect size of 0.22). Accounting for multiple comparisons of proportions (the proportion of optometry accuracy) for treatments vs. a control [24], the overall alpha is set to be 0.05, thus a level of significance is 0.0167 (0.05/3) by using Bonferroni adjustments. In this study, we set the power of each test at 0.9, all groups have the same sample size. And finally, a total of 456 USP visits is required, each OSP is corresponded to a USP visit. Considering 5% of dropout and/or missing data, the number of participants adds up to a total of 480 participants. The sample size required for the control group and each of the intervention group is 120 respectively. The sample size calculation was performed using PASS 15 software (NCSS, Kaysville, UT, USA).

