### Statistical analysis plan

Data will be analyzed on an intention-to-treat (ITT) basis to compare primary and secondary outcomes in the originally assigned groups. Baseline characteristics for each group will be descriptively presented using mean (standard deviation, SD) or median (interquartile range, IQR) for continuous variables depending on the distribution, and frequency (percent) for categorical variables.

Primary outcome (optometry accuracy) and secondary outcomes will be analysed using generalized linear models (GLMs). Binomial distribution and identity link function will be used for binary outcomes, Poisson distribution and identity link function will be used for count outcomes, and normal distribution and identity link function will be used for continuous outcomes. Effects (risk differences for binary and count outcomes, and mean differences for continuous outcomes) with corresponding two-sided 95% confidence intervals will be estimated. Missing data will be imputed using multiple imputation in the GLMs.

Sensitivity analysis will be performed by covariate-adjusted analysis using GLMs with baseline characteristics as covariates. Cost-effectiveness analyses will be performed, and cost-effectiveness ratios will be calculated using bootstrapping techniques. Statistical significance will be considered to be present when the P value is < 0.05. Subgroup analyses will be performed, based on the type of service (hospitals and optical shops) and types of practitioners (such as licensed vs. unlicensed practitioners). IBM SPSS (version 20) and SAS (version 9.4, SAS Institute) will be used for all statistical analyses.

Subgroup analyses will be performed, based on type of service (hospitals and optical shops) and types of practitioners (such as licensed vs. unlicensed practitioners).

We expect the number of withdrawals to be low because the intervention is delivered by the USP and the service provider will receive the intervention passively. Additionally, the intervention will be conducted over a brief period of one USP visit thus without post-visit follow-ups. All data will be entered into the REDCap system immediately after the visit. Thus, we expect to have minimum (if any) missing data. A maximum dropout and/or missing data of 5% is considered in our sample size calculation. We will analyze the data according to the ITT principle.

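### The Bonferroni level of 0.0167 set for the three primary comparisons is not carried into the analysis section, which declares significance at P < 0.05 without exception

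*Protocol article*

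**What the plan says.** The design compares "three intervention groups versus a common control group" (Study design and setting). The Sample size calculation section recognises what follows from this: "Accounting for multiple comparisons of proportions (the proportion of optometry accuracy) for treatments vs. a control", "the overall alpha is set to be 0.05", "thus a level of significance is 0.0167 (0.05/3) by using Bonferroni adjustments". It does not say whether the 0.0167 is one-sided or two-sided.

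The Statistical analysis plan section covers primary and secondary outcomes together, using generalized linear models. Effects "with corresponding two-sided 95% confidence intervals will be estimated". The threshold is then given once: "Statistical significance will be considered to be present when the P value is < 0.05". That section mentions no adjusted P value, testing order or separate level for the primary outcome. The 0.0167 appears only in the sample size section.

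**The concern.** The article prints two levels for the same three tests. An analyst working from the sample size section would require P < 0.0167 for each BVI; one working from the analysis section would require P < 0.05. On the same data they could reach opposite conclusions about a BVI.

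At stake is the chance that at least one ineffective BVI is declared effective. The sample size section promises to hold that chance at 5%, and the printed decision rule does not. The Discussion expects the results to inform policy-makers and to be usable by patients themselves, so a false claim for a single BVI matters. The stated power also refers to a different test from the one the analysis section describes.

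**Working it through.** **Inputs.** From Sample size calculation: control proportion 0.441, intervention proportion 0.661 (difference 0.22), power 0.90 per test, overall alpha 0.05, per-test level 0.05/3 = 0.0167, 456 visits before and 480 after 5% loss. From Allocation and blinding: 1:1:1:1 allocation. From Statistical analysis plan: P < 0.05 and two-sided 95% intervals.

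**1. The plan's own figure.** Two-proportion z-test with unpooled variance:

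n = (z_α + z_β)² × [p1(1−p1) + p2(1−p2)] / (p2−p1)²

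The variance sum is 0.2465 + 0.2241 = 0.4706.

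- One-sided 0.0167: (2.128 + 1.282)² × 0.4706 / 0.0484 = 113.03, so 114 per arm and 4 × 114 = 456. This matches exactly, and 456/0.95 = 480.
- Two-sided 0.0167: (2.394 + 1.282)² × 0.4706 / 0.0484 = 131.4, so 132 per arm, 528 in total.

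Other variants:

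| Level | Variance | Per arm | Total |
|---|---|---|---|
| 0.0167 one-sided | pooled | 117 | 468 |
| 0.0167 two-sided | pooled | 136 | 544 |
| 0.0167 two-sided | continuity-corrected | 145 | 580 |
| 0.05 two-sided | unpooled | 103 | 412 |
| 0.05 two-sided | pooled | 106 | 424 |
| 0.05 two-sided | continuity-corrected | 115 | 460 |

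The last row comes close to 456, but not at the level the article states. At 0.0167, the one-sided calculation is the only one that fits.

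**2. Family-wise error.** With equal arms and a shared control, any two of the three z-statistics have correlation 0.5. With no BVI effective, and φ and Φ the standard normal density and distribution function,

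FWER(c) = 1 − ∫ φ(u) × [Φ((c − √0.5·u)/√0.5) − Φ((−c − √0.5·u)/√0.5)]³ du

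- Two-sided 0.05, c = 1.960: 12.5%.
- Two-sided 0.0167, c = 2.394: 4.5%.
- Exact Dunnett: c = 2.349, which is 0.0188 per comparison, for 5.0%.

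Treating the three tests as independent gives 1 − 0.95³ = 14.3% and 1 − (1 − 0.0167)³ = 4.9%. Simulated binomial data at 44.1% in every arm, tested with unpooled variance, give 13.2% (114 per arm) and 13.7% (120) at 0.05. At 0.0167 they give 5.1% and 4.5%. The normal result of 12.5% is therefore not an overstatement. Relative to the stated level, 12.5/5 = 2.5.

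**3. Where the two rules disagree.** At 120 per arm and the planned proportions, the standard error of the difference is √(0.4706/120) = 0.0626. The smallest significant difference is 1.960 × 0.0626 = 12.3 percentage points at 0.05 and 2.394 × 0.0626 = 15.0 at 0.0167. An observed difference between these is positive under one section and not under the other.

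**4. Power if 0.0167 is applied two-sided.** Unpooled: Φ(0.22/SE − 2.394).

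- 114 per arm, SE 0.0642: 84.9% (pooled variance 83.4%).
- 120 per arm, SE 0.0626: 86.8% (pooled variance 85.5%).

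**5. Interval width.** 2.394/1.960 = 1.22. The matching level is 1 − 0.05/3 = 98.33%.

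**The case against.** The strongest defence is that the two sections can be read together. The sample size section gives a specific rule for the primary outcome. The analysis section's threshold is generic, comes after the sensitivity and cost-effectiveness analyses, and names no outcome. The specific rule might govern the three primary tests and the generic one the rest, or 0.05 might mean the overall level. This is a possible intention, and for that reason a reader should not infer that the investigators have dropped error control. The article does not say so. But it does not state either rescuing reading, and the unrestricted sentence is its only decision rule. Nor is this detail left to an unseen analysis plan, because a threshold is printed and it differs from the one the design used.

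It is also fair to say that 95% intervals are ordinary estimation reporting and can stand beside adjusted tests. A reader might take them as a second decision rule, but the article does not use them that way. The case rests on the P-value threshold, and intervals at the matching level are a matter of consistent reporting.

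A third objection stands in full: adopting two-sided 0.0167 costs more than one added sentence, because it does not deliver the stated 90% power at the stated N. A reader might go further and infer that the sample size is wrong or must rise to 528. The documents do not support that. Sidedness is not stated, the one-sided origin of 456 is inferred from the match, and power stays above 80% at the assumed effect.

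**Conclusion.** The point holds as an unreconciled conflict between two printed rules for the primary comparisons, and it should be settled before results are seen. Followed literally, the analysis section gives about 12.5% family-wise error, roughly 2.5 times the stated 5%. The design's own 0.0167, applied two-sided, gives about 4.5%.

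These figures assume that no BVI has an effect, equal arms, a shared control and independent visits. Independence is an assumption, since the Allocation and blinding section has each USP visit providers in all four groups. The 12.5% covers only the three primary comparisons. It should not be read as the error rate over secondary outcomes and subgroups, to which the sample size section never extended its adjustment.

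**What to change.** In the Statistical analysis plan section, state that each of the three primary BVI-versus-control comparisons is tested two-sided at 0.0167 and reported with a 98.33% confidence interval. Dunnett-adjusted P values and intervals judged against an overall 0.05 are an equivalent choice. Holm would serve for P values only, since it has no simple matching intervals. P < 0.05 and 95% intervals can remain for the other analyses.

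In the Sample size calculation section, state the sidedness. With the two-sided rule, restate power per comparison as about 83–85% at 114 per arm and 86–87% at 120 per arm, in place of 90%. N stays at 480.

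The cost is two short text changes, primary intervals about 22% wider with Bonferroni, and a lower stated power.

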### Participants and recruitment

OSPs are not informed of participation, thus they will be visited unannounced by USP. We will recruit USPs and train them, implementing interventions in different groups. Figure 1 presents an explicit flow chart of this study.

The study subjects (OSPs and their refraction-ists) must meet the following criteria to be eligible for the study: (1) OSPs in Guangzhou and Inner Mongolia, consisting of general hospitals with ophthalmology department, ophthalmology specialty hospitals or clinics, and optical shops; (2) any personnel providing optometry services, as licensed optometrists and ophthalmologists or not, at the above-mentioned institutions. Exclusion criteria include: (1) providers providing Internet-based services only; (2) providers providing optometry service solely for contact lenses only.

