### Allocation and blinding

The sample of OSPs will be randomly assigned to the control or the intervention groups with a 1:1:1:1 allocation. The randomization schedule will be computer-generated and stratified by service type (such as hospitals and optical shops). A stratified randomization is used to ensure that the four groups have a similar distribution in type as this characteristic may substantially affect the outcomes.

The allocation of OSPs will be conducted by a statistician otherwise not related to the research. Other than a code for each service provider and the service type, the statistician will have no other identifying information of the sampled participants.

After stratified random sampling, the allocation sequence will be generated by computer, and the randomization for each group will be initiated by the researcher. The USPs will be enrolled by the researcher and assigned randomly to the OSPs in each group. To balance confounding factor of individual USP, each USP will be assigned to four groups for equal visits.

The study subjects (OSPs) will be blinded to their allocation status as we have obtained a waiver for their informed consent. The USPs will not be blinded as they will need to implement BVIs according to the allocation status. The outcome assessors and data analysts will be blinded to reduce subjective analysis.

As no informed consent will be sought, unblinding on the side of OSPs is highly unlikely if possible at all. But if that occurs, a replacement of provider with similar characteristics will be identified for a replacement visit.

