### Brief verbal interventions

The USP will execute three different forms of BVIs. For each, the USP will deliver exactly the same rendition of the USP cases other than a proactive line before undergoing the eye examination that represents the content of an assigned BVI. The three BVIs are informed by three respective underlying theories: qualification requirement, patient knowledge and social monitoring. In Group A, the USPs will say “I would like to ask for a qualified professional to do the examination/optometry.” or something like that, to create a qualification requirement for better service. In Group B, the USPs will say “I learned from the Internet that subjective refraction is a critical component” to show patients’ knowledge of appropriate procedures. In Group C, the USPs will say “I am a blogger and will share my experience on the Internet” to create a scenario of social monitoring. Except for the first opening statement and BVI, the USPs will not offer any other lines unless prompted by a provider’s question or instruction. They will also provide only standard answers and responses, strictly according to the USP scripts.

BVIs are brief interventions that will be started and concluded with a single USP visit, so we expect few or no cases of discontinuing an allocated intervention. In the case a provider refuses to provide optometry service, the USP will record the reason and visit a replacement provider with similar characteristics.

The intervention will be delivered by highly trained USPs even though they are also real patients. Actually, USP and companion will be trained together, and then always work together. They will be paired according to their free time. The intervention in the study is instant and involves no follow-ups. We will ensure that all participants receive adequate training to ensure the smooth execution of the study. Meanwhile, we will check the quality of USPs’ renditions of their roles and scripts through the voice recordings that the USPs will take with their smartphones during each optical visit. Thus, we expect a high level of adherence to the research protocols, and we will provide feedback to the USPs within 48 h if they do not adhere to the protocols, in order to improve their adherence in further visits.

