### Data collection and management

We will collect a variety of eye care quality information and other related explanatory variables. Donabedian’s classification of quality of care (structure, process and outcome) will be used for quality evaluation [31]. The quality of structure level includes: personnel qualification (whether the practitioner is qualified and professionally certified) and equipment layout (whether the facility’s hardware meet the requirements of optometry and whether its layout is appropriate), etc. This kind of information will be obtained from publicly available websites, promotional materials and USP on-site observations.

Almost all data will be collected through the USP visit to the OSPs. The USP will visit each provider along with a companion as “friend”. While the USP is under examination by the practitioner, the companion will observe the equipment environment and the optometry procedures. At the end of each visit, the USP will ask for a spectacle prescription. The USP and the companion will work together to complete the quality checklist and other data forms on the smartphone within 15 min of the end of the optometry service. We assure that all collected data will be securely stored and protected in accordance with relevant privacy regulations and guidelines.

All data collected will be entered into the Research Electronic Data Capture (REDCap) system by USP companions. REDCap is a free and powerful cloud-based tool for data collection, storage and management [32]. It will also track any changes to the data in an audit trail and be able to fully de-identify the data. REDCap has bank-level security features, and only the investigators involved in this study can access the data. All forms collected for this study, including the signed consent forms, will be stored on REDCap system safely and conveniently.

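### The licensed-versus-unlicensed subgroup rests on a characteristic recorded at least partly after randomisation, which Group A's line may change; within-licence comparisons of Group A with control are then not randomised comparisons

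*Protocol article*

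**What the plan says.** All references are to the protocol article.

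- **Statistical analysis plan.** Subgroup analyses are planned by type of service and by "types of practitioners (such as licensed vs. unlicensed practitioners"). The sentence appears twice. Neither version ties licence status to a time before the visit or treats Group A separately.
- **Allocation and blinding.** "The sample of OSPs will be randomly assigned to the control or the intervention groups with a 1:1:1:1 allocation". Randomisation is stratified by service type only.
- **Participants and recruitment.** Eligible examiners are "any personnel providing optometry services, as licensed optometrists and ophthalmologists or not, at the above-mentioned institutions". One provider may therefore have both licensed and unlicensed staff.
- **Brief verbal interventions.** Each intervention is "a proactive line before undergoing the eye examination that represents the content of an assigned BVI". Group A's line is "I would like to ask for a qualified professional to do the examination/optometry", and its stated aim is "to create a qualification requirement for better service".
- **Data collection and management.** Qualification is defined for the individual: "personnel qualification (whether the practitioner is qualified and professionally certified"). On sources: "This kind of information will be obtained from publicly available websites, promotional materials and USP on-site observations".
- **Discussion.** Structural elements of the providers are named among the outcomes. Data collection and management places personnel qualification under structure, so the same item serves as both a result and a subgroup factor.

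**The concern.** A subgroup comparison keeps the protection of randomisation when the factor is fixed before allocation, or at least cannot be changed by the intervention. Service type meets this condition. The licence status of the person who examines may not, because Group A's line asks for exactly that to change.

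If some providers respond by bringing in a licensed colleague, the licensed stratum of Group A contains providers whose control counterparts sit in the unlicensed stratum. Two things follow. Any benefit that comes from the change of examiner disappears from within-stratum comparisons. The strata also hold different mixes of providers in the two arms, so a difference can appear that the line did not cause.

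At stake is the reading of Group A. Its subgroup table could show nothing, or apparent harm, in both licence groups beside a positive overall result.

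**Working it through.** **What can be anchored.** The plan gives no figure for this subgroup, so there is none to reproduce. The Sample size calculation section assumes accuracy of 44.1% in control and 66.1% under intervention (66.1 − 44.1 = 22.0 points, as stated). Those two values anchor the illustration. All licence shares and stratum accuracies below are assumptions.

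**Set-up.** Divide providers into three types: always a licensed examiner (share w_A), licensed only if asked (switchers, w_S) and never licensed (w_N). Suppose the line acts only by changing the examiner. Accuracy is then a for always-licensed and n for never-licensed providers in both arms. Switchers have accuracy c in control and t in Group A.

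- True overall effect = w_S × (t − c)
- Apparent effect, licensed = (w_A·a + w_S·t)/(w_A + w_S) − a = [w_S/(w_A + w_S)] × (t − a)
- Apparent effect, unlicensed = n − (w_S·c + w_N·n)/(w_S + w_N) = [w_S/(w_S + w_N)] × (n − c)

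The true effect depends on t − c. The subgroup effects depend on t − a and n − c, which compare different providers.

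**1. Removal of the mediated effect.** Let accuracy depend only on licence: 77.1% licensed, 22.1% unlicensed. The licensed share is 40% in control and 80% in Group A.

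- Control: 0.40 × 0.771 + 0.60 × 0.221 = 0.441
- Group A: 0.80 × 0.771 + 0.20 × 0.221 = 0.661
- Overall effect +22.0 points; within each licence stratum, 0.

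This is not selection bias. Zero is the correct effect with the examiner's licence held fixed; the mistake would be to read it as absence of benefit.

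**2. Selection, over a range of switching shares.** Control accuracy is 44.1% in every row, and w_A = 40%.

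| Switchers | a | c → t | n | True overall | Licensed | Unlicensed |
|---|---|---|---|---|---|---|
| 40% | 65% | 35% → 60% | 20.5% | +10.0 | −2.5 | −9.7 |
| 30% | 60% | 40% → 55% | 27% | +4.5 | −2.1 | −6.5 |
| 20% | 60% | 45% → 55% | 27.75% | +2.0 | −1.7 | −5.7 |
| 10% | 60% | 45% → 55% | 31.2% | +1.0 | −1.0 | −2.3 |

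First row in full: overall 0.40 × (0.60 − 0.35) = +0.100; licensed (0.40/0.80) × (0.60 − 0.65) = −0.025; unlicensed (0.40/0.60) × (0.205 − 0.35) = −0.097.

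**3. The sign can reverse.** In the first row, exchange the control accuracies of switchers and never-licensed providers (c = 20.5%, n = 35%). The unlicensed stratum then shows (0.40/0.60) × (0.35 − 0.205) = +9.7 points, although the line did nothing for the never-licensed providers who make up that stratum in Group A.

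**4. No switching.** With w_S = 0, and a direct 5-point gain at all providers, licensed accuracy goes from 60% to 65% and unlicensed from 33.5% to 38.5%. Both subgroups recover +5.0.

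**The case against.** The strongest reply is that nothing in the protocol shows that the line changes the examiner. It does not say when the examiner is assigned, how many practitioners a provider has, or how often a switch is possible. The Control group section notes that some hospital visits need advance online registration. This stands: a reader might infer that the subgroup is biased outright, and the documents support only a conditional statement.

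Four further inferences also go too far.

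- *That all three comparisons are compromised.* Group B's line concerns subjective refraction and Group C's concerns sharing the experience online. Neither asks for a different examiner, so for them effect modification by licence is a fair question unless their lines also alter who examines.
- *That a real benefit would be hidden from the trial.* It would still show in the primary intention-to-treat comparison, which this subgroup does not touch.
- *That licences will be noticed more often in Group A.* This is possible, because the standardised patients are unblinded and have raised qualification. But the line does not ask to see a licence, and websites and promotional materials are also sources.
- *That the covariate-adjusted sensitivity analysis has the same flaw.* Its baseline characteristics are not listed; the flaw arises only if examiner licence is among them.

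It can also be said that the wording offers licence only as an example and that an unseen analysis plan may define it. This does not remove the point. The article names the factor twice, defines qualification for the individual practitioner, records it partly at the visit, and nowhere limits it to status known beforehand.

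**Conclusion.** The point holds in conditional form, for Group A against control. As written, the plan permits subgrouping on a characteristic recorded partly after randomisation, which that arm's line asks the provider to change. To the extent that the examiner does change, the within-licence comparisons lose the mediated part of the effect and may carry selection bias of either sign.

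The size cannot be stated from the documents, because it depends on the switching rate and on how switching providers differ from the rest. Under the assumed values the distortion runs from none at zero switching to the loss of the whole 22-point effect in both strata. The service-type subgroup stands as planned. This should be corrected, but it does not threaten the main result.

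**What to change.** 1. State that the licence status of the examiner, as observed at the visit, will not be a subgroup factor or baseline covariate for Group A against control.
2. Define any practitioner-type subgroup from provider-level staffing or licensing information fixed before randomisation, for example from the public sources that the protocol already lists. If that is not feasible, drop this subgroup.
3. Report, by arm, whether a licensed practitioner performed the refraction, as a secondary outcome; Table 2 does not list it now. This also shows whether the mix of examiners differs between arms, including Groups B and C. Otherwise use the variable only in an analysis labelled as mediation.

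The cost is mainly wording, since practitioner qualification is already to be collected. Licensing information available before the visit may be incomplete, so the subgroup may be coarser or may have to be given up.
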